### Study aims

Building on the current gaps in the literature, we designed a triple-blind, randomized, placebo-controlled trial to examine the role of SCFAs as mediators of microbiota-gut-brain interactions in AN. Specifically, we aim to assess the effects of SCFAs on the acute stress response, eating behavior, and nutritional status in patients with AN following SCFA delivery to the large intestine using pH-dependent colon-delivery capsules (CDCs). This method allows the administration of SCFAs in exact amounts in a chronically tolerable manner while mimicking, as closely as possible, the process of bacterial fermentation of dietary fiber in the gut. We hypothesize that colonic SCFA administration daily for six weeks will modulate neuroendocrine [cortisol, adrenocorticotropin hormone (ACTH), salivary-alpha amylase], cardiovascular (heart rate, heart rate variability), and emotional responses (subjective stress, anxiety, perceived control, hunger and desire to eat) to acute laboratory stress. Additionally, we predict that the intervention will result in a shift in dietary choices towards less restricted choices, as captured during a food choice task (FCT), and an improvement in the nutritional state, reflected by a greater increase in BMI.

The longitudinal design of this study provides a unique opportunity to examine the causal role of SCFAs in stress and eating behaviors in individuals with AN. By stepping away from the typical cross-sectional studies in the gut microbiota research field, our work can yield new insights into the complex interplay between the gut, stress system, and eating behavior and facilitate new therapeutic targets for stress-related psychiatric disorders.

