### Statistical analysis

#### Statistical methods for primary and secondary outcomes

The primary and secondary outcome variables will be analyzed using linear mixed models with “group” (placebo or SCFAs) as a between-subject factor and “visit” (pre- or postintervention) and, where appropriate, “timepoint” (measurement point within each visit) as within-subject factors. The group-by-visit and the group-by-visit-by-timepoint interaction effects constitute the principal effects of interest. If participants fail to exhibit an elevated cortisol stress response following stress induction, we will exclude their data from the analysis. To investigate the effect of the SCFAs intervention on treatment response, we will further control for BMI by including changes in BMI between visits 1, 2, and 3 in the linear mixed model as a continuous covariate. To investigate whether the changes in circulating SCFAs levels are mediated by the changes in the cortisol stress response to our stressor, we will pool all stress responders and enter the change in SCFA levels (post-intervention—pre-intervention) into the linear mixed model as a continuous covariate, including its interaction with visit, while omitting the group variable. The chosen significance level is alpha = 0.05. Follow-up planned contrasts will be conducted if there is a significant interaction effect and will be corrected for multiple testing comparisons using step-down Bonferroni (Holm) adjustment. Data of the intervention group will be further exploratively analyzed using linear mixed models with restrictive type AN and binge/purge type AN as “patient group,” investigating differences between the intervention of SCFAs between subtypes of patients with AN. In addition, we will enter the changes in questionnaires (baseline, post-intervention) into a linear mixed model as continuous covariates to investigate in an explorative way whether these changes (e.g., in AN severity, affect changes, subjective stress, etc.) are mediated by the changes in SCFAs levels and microbiota composition.

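### The SCFA–cortisol mediation question is worded backwards, and its model drops treatment group, so the analysis cannot support a mediation conclusion

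*Protocol article*

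**What the plan says.** All of this is in the protocol article.

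- **Aim** (Study aims): the trial is to "examine the role of SCFAs as mediators of microbiota-gut-brain interactions in AN". The hypothesis that follows is that colonic SCFA delivery changes the stress response, cortisol included.
- **Question for the SCFA–cortisol analysis** (Statistical methods for primary and secondary outcomes): "To investigate whether the changes in circulating SCFAs levels are mediated by the changes in the cortisol stress response to our stressor".
- **Model for that question** (same sentence): the data are those of the stress responders from the two arms combined. SCFA change, post minus pre, is a covariate in the mixed model, together with its product with visit. Treatment does not appear, since the model is fitted "while omitting the group variable".
- **Questionnaire analysis** (end of the same paragraph): the plan will "enter the changes in questionnaires (baseline, post-intervention) into a linear mixed model as continuous covariates". The stated purpose is to explore mediation of those changes by SCFA levels and the microbiota.

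The AN-subtype and questionnaire analyses are labelled explorative. The SCFA–cortisol analysis is not.

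**The concern.** There are two faults.

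**Direction.** As worded, the question is whether the cortisol response carries a change in SCFA levels. The trial asks whether SCFAs carry an effect to the cortisol response. The model follows the trial's order, so the sentence disagrees with its own model.

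**Group.** A mediation claim has to separate two explanations. Either the capsules change circulating SCFA, which then changes cortisol, or the capsules change circulating SCFA and, by some other route, also change cortisol. With group left out, assignment is a possible common cause of both changes, and the pooled slope mixes the two explanations. The second is not far-fetched on the protocol's own account, because the Background lists several pathways for SCFA action, neural among them.

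At stake is the claim that the effect on cortisol runs through circulating SCFA. A significant pooled slope could be reported as mediation when it shows only that the arms differ on two variables.

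**Working it through.** **1. The passages side by side**

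| Place | Mediator | Outcome |
|---|---|---|
| Study aims | SCFA | stress response |
| SCFA–cortisol question | cortisol response | SCFA change |
| SCFA–cortisol model | none named; SCFA change is predictor | cortisol |
| Questionnaire question | SCFA and microbiota | questionnaire change |
| Questionnaire model | none named; questionnaire change is covariate | not stated |

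The SCFA–cortisol question is the only row with cortisol as mediator. The pooled fit cannot settle the direction either. Regressing cortisol on SCFA or SCFA on cortisol gives the same p-value (0.00036 both ways in one test dataset).

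**2. The plan's own figure, used to set a scale**

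The protocol gives no figure for this analysis. Its sensitivity calculation has 40 per arm, f = 0.16 and 80% power for the 2 × 2 interaction. The correlation ρ between visits is not stated; take 0.5.

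- λ = f² × N × m / (1 − ρ) = 0.0256 × 80 × 2 / 0.5 = 8.192 on (1, 78) df, giving power 80.7%. The stated 80% is reproduced. (ρ = 0.3 gives 66.6%; ρ = 0.7 gives 95.4%.)
- The same effect on the change score is d = 2 × √(f² × 2 / (1 − ρ)) = 2 × √0.1024 = 0.64 SD.

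A treatment effect of about 0.63 to 0.64 SD on cortisol change is therefore the size the trial says it can detect, given ρ = 0.5.

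**3. What the pooled model estimates when SCFA has no effect on cortisol**

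With two visits, the SCFA-change-by-visit term is the slope of cortisol change on SCFA change. Let treatment move SCFA change by *a* SD and cortisol change by *c* SD through other routes, with 1:1 allocation and no SCFA-to-cortisol path. In absolute value the pooled correlation is

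r = (a·c/4) / √[(1 + a²/4)(1 + c²/4)].

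It is zero only if *a* or *c* is zero. With group in the model, the expected SCFA slope is zero for any *a* and *c*.

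Example: a = 2, c = 0.634, n = 78 (92 × 0.85 = 78.2). Then r = 0.317 / √(2 × 1.1005) = 0.214. By Fisher's z, atanh(0.214) × √75 ≈ 1.88, and the chance of p < 0.05 is about Φ(1.88 − 1.96) ≈ 47%.

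**4. Simulated false-positive rates, group omitted as planned**

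| n | c (SD) | a = 0.5 | a = 1 | a = 2 | a = 3 |
|---|---|---|---|---|---|
| 78 | 0.63 | 9% | 23% | 48% | 61% |
| 60 responders (assumed) | 0.63 | 9% | 19% | 38% | 51% |
| 80 | 0.64 | 10% | 23% | 49% | 65% |
| 80 | 1.0 | 17% | 44% | 85% | 95% |

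The rows come from separate runs, so differences of a point or two are simulation noise. With c = 0 or a = 0 the rate is about 4 to 5.5%. With group kept it is 4.2 to 5.9% in every setting. A two-visit random-intercept mixed model gave 47% at a = 2, c = 0.64 and 5.3% at a = 2, c = 0 (n = 80), so the result does not come from using change scores.

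**The case against.** Several points can fairly be made for the plan.

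- **The reversal is in the wording only.** A reader might infer that the analysis itself runs backwards. It does not, because SCFA change is the predictor. This stands, and the point is limited to a sentence that contradicts its own model.
- **Inflation is conditional.** A reader might infer that this analysis often gives false positives. The documents do not support that. It takes both an SCFA rise and an effect on cortisol by another route, and the protocol gives no size for either. The Background lists pathways but does not say that they bypass the circulation. This stands, so the rates above are a range under assumptions.
- **The trial's main aim does not hang on this model.** A reader might infer that the hypothesis about SCFAs would be answered by a confounded correlation. The effect of SCFA delivery is tested by the group-by-visit and group-by-visit-by-timepoint terms, which keep group. This stands.
- **The questionnaire analysis is different.** It words mediation in the expected order, is labelled explorative and does not say that group is dropped. Only its placing of the supposed outcome among the covariates is at odds with its question.
- **Pooling uses the full range of SCFA levels.** This is a reason for an exploratory association, not for a mediation claim.
- **An article may leave the indirect-effect method to the full plan.** That is fair, and its absence is not the fault. The express omission of group is.

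**Conclusion.** The point holds in limited form. The question is stated in the wrong direction, against the Study aims and against its own model. Because group is expressly left out, the analysis as written cannot distinguish mediation by circulating SCFA from a treatment that changes SCFA and cortisol separately.

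If treatment shifts cortisol by about 0.63 SD outside circulating SCFA and raises serum SCFA by 0.5 to 3 SD, the false-positive rate at n = 78 runs from about 9% to 61%, against about 5% with group kept. It stays near 5% if either effect is absent. These figures rest on assumed effect sizes, on ρ = 0.5 for the link to f = 0.16, and on a true SCFA-to-cortisol path of zero.

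The fault lies in a supplementary mechanistic analysis. It is worth correcting, but it does not touch the primary comparison.

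**What to change.** 1. Reword the question as: whether the effect of SCFA treatment on the cortisol response is mediated by change in circulating SCFAs.
2. Keep group and its interaction with visit in the model alongside SCFA change and its interaction with visit.
3. Report the indirect effect with a bootstrap interval. It is the effect of group on SCFA change, times the effect of SCFA change on cortisol adjusted for group and baseline values.
4. Label it exploratory. SCFA change is not randomised, so keeping group removes confounding by assignment only; diet or BMI change may still confound the SCFA–cortisol path.
5. If the pooled model is preferred, call it an exploratory association and drop the mediation claim.
6. Separately, in the questionnaire analysis make the questionnaire change the outcome, with SCFA and microbiota changes as predictors, to match its stated question.

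The cost is rewording and a few extra model fits. Serum SCFA is already sampled at both visits (Biological samples). The statistical price is a wider interval for the SCFA slope. At equal residual cortisol SD the standard error grows by about √(1 + a²/4), which is 1.12 times at a = 1 and 1.41 times at a = 2. The narrower pooled interval comes from the between-arm contrast, which is the part that cannot be read as mediation.

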Short-chain fatty acids (SCFAs), metabolites produced following the bacterial fermentation of dietary fiber in the large intestine, are considered candidate mediators of the gut bacteria's effects on the host [17]. Acetate, propionate, and butyrate are the most abundant SCFAs and may affect the host through immune, endocrine, neural, and humoral pathways [18]. Stress is the physiological response to a challenging physical, emotional, or cognitive encounter that exceeds the body's coping resources and activates the sympatho-adrenal medullary pathway (SAM) and the hypothalamus–pituitary–adrenal (HPA) axis. Interestingly, recent evidence suggests that SCFAs mediate the effects of gut bacteria on stress responses of the HPA axis [19–21]. Oral supplementation of SCFAs in rodents reduced corticosteroid response to acute stress, reduced stress-induced gastrointestinal permeability, and reversed changes in anhedonia [20, 21]. Human translational research found that administering SCFAs to the large intestine attenuated the cortisol response to acute psychosocial stress [19]. While the stress response can be adaptive and beneficial, prolonged or exaggerated stress can heighten the risk of developing neuropsychiatric disorders [22]. The involvement of the HPA axis in individuals with AN has been implicated in the development and perpetuation of this disorder [23–26]. Researchers hypothesize that eating disorder-related behaviors, such as restricting, binging, purging, or excessive physical exercise, may function as dysfunctional adaptations to alleviate and manage negative affective states [27–29]. These maladaptive eating behaviors often increase in response to stress and negative emotions [30, 31]. This consequently forms a vicious cycle, where the continued physiological state of nutritional deprivation can lead to subjective and objective stress activation (e.g., via chronic HPA axis stimulation and autonomic nervous system alterations) [23, 32, 33]. The possible role that the gut microbiota and SCFAs might play in the maladaptive stress responses and related eating behaviors characteristic of AN is intriguing and presents a promising research avenue to expand our understanding of this complex disorder.

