## Outcomes

### Primary and secondary outcomes

The primary outcome of this study focuses on the salivary cortisol response to acute laboratory stress. We will examine the change in cortisol levels within and between SCFAs and placebo groups. Crucial secondary outcomes encompass the participants' food choices and nutritional status (BMI). All other measures delineated in the subsequent sections serve as secondary outcome measures. See Table 1 for an overview of scheduled assessments.

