### Measurements related to the TSST

#### Neuroendocrine measures

To measure the adrenocortical stress response during the TSST, we will collect eight saliva and four blood samples at regular intervals before, during, and after stress induction (see Fig. 3). Saliva samples will be obtained using synthetic Salivette devices and will be used to determine salivary cortisol and alpha-amylase (sAA) levels. Blood samples will be collected through an IV catheter in EDTA tubes to measure ACTH levels. After collection, all samples will be centrifuged and stored at − 80 °C until analysis by ELISA. Additionally, the participants' menstrual cycle phase and any use of hormonal contraceptives will be noted for its effect on the salivary cortisol response to acute stress.

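### The supplementary SCFA–cortisol model names only an SCFA-change-by-visit interaction, which on raw samples tests mean cortisol and does not isolate the stress response

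*Protocol article*

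**What the plan says.** Under Primary and secondary outcomes, the protocol article states: "The primary outcome of this study focuses on the salivary cortisol response to acute laboratory stress". Under Neuroendocrine measures, for the Trier Social Stress Test: "we will collect eight saliva and four blood samples at regular intervals before, during, and after stress induction".

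Under Statistical methods for primary and secondary outcomes, the linear mixed model has group, visit and, where appropriate, timepoint. For the randomised comparison: "The group-by-visit and the group-by-visit-by-timepoint interaction effects constitute the principal effects of interest".

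The same paragraph then describes a supplementary model whose target is "the changes in the cortisol stress response to our stressor". Stress responders from both arms are pooled, group is dropped, and the post-minus-pre change in SCFA enters "as a continuous covariate, including its interaction with visit". No timepoint interaction is named for SCFA change. The article defines no area under the curve, peak-minus-baseline or other single-number cortisol response.

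**The concern.** The target is a change in the stress response, that is, in the rise over the pre-stress level. With samples taken before, during and after stress as the outcome, an interaction with visit alone concerns the average of all of them. The paragraph distinguishes the two-way from the three-way term for group, yet gives only the two-way term for SCFA change.

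This matters because both arms undergo nutritional rehabilitation between the two visits. The Background section says that "nutritional deprivation can lead to subjective and objective stress activation (e.g., via chronic HPA axis stimulation", and it ties dietary fibre to SCFA production. Renourishment could plausibly move basal cortisol and circulating SCFA together without any change in stress reactivity. Because the arms are pooled and group is omitted, randomisation does not protect this association. A shared drift in level could then be reported as a link between SCFA and the stress response, which is the trial's mechanistic claim.

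The point is separate from the direction of the mediation sentence and from the omission of group. With both corrected, the named term would still not isolate the response.

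**Working it through.** **No figure to reproduce for this model.** The article gives no power figure for it. Its 80% power (f = 0.16, 40 per arm) concerns the visit-by-treatment interaction. It reproduces as 80.7% if the correlation between visits is 0.5 (an assumption): λ = 0.16² × 80 × 2 / (1 − 0.5) = 8.19 on 1 and 78 df. It has no bearing here.

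**What the named term estimates.** Let x be a participant's SCFA change and d_t the post-minus-pre cortisol difference at sample t (t = 1 to 8). With complete data, SCFA-change-by-visit is the slope of the mean of d_1 to d_8 on x. Write d_t = L + R·s_t + e_t, where L is a level shift between visits, R the change in the response, s_t the response curve and e_t residual. Then:

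- mean over all samples = L + R·s̄ + ē, which mixes level and response;
- post-stress minus pre-stress contrast = R × (difference in s) + residual, from which L cancels.

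This step needs no assumed numbers.

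**Illustration.** None of these inputs is in the article; all are assumed: 64 responders (80% of 80); curve s = 0, 0, 0.3, 0.8, 1, 0.7, 0.4, 0.2; SD of R = 1; residual SD 0.5 per sample at each visit, so residual variance 0.5 per difference. The comparator contrast is the mean of samples 4–6 minus the mean of samples 1–2.

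- s̄ = 3.4/8 = 0.425; contrast weight on R = 2.5/3 = 0.833.
- Residual variance of the mean = 0.5/8 = 0.0625; of the contrast = 0.5 × (1/3 + 1/2) = 0.417.

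*Case A: SCFA change correlates 0.35 with R only.* The correlation with the mean is 0.35 × 0.425 / √(SD_L² + 0.425² + 0.0625). With the contrast it is 0.35 × 0.833 / √(0.833² + 0.417) = 0.28, whatever SD_L is.

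| SD of L | Correlation with mean | Power, visit term | Power, 1-df contrast | Power, 7-df three-way test (unstructured covariance) |
|---|---|---|---|---|
| 0.5 | 0.21 | 39% | about 60% | 32% |
| 1.0 | 0.13 | 17% | about 60% | 30% |
| 1.5 | 0.09 | 12% | about 60% | 30% |

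If the residual SD is instead 0.5 per difference, the contrast reaches about 70% and the visit term barely changes (40%, 17%, 11%). With no level variation at all, under that smaller residual, the visit term does slightly better than the contrast (75% against 70%).

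*Case B: SCFA change correlates with L only (SD of L = 1).* The correlation with the mean is r / √(1 + 0.425² + 0.0625) = r / 1.115, giving 0.18, 0.27 and 0.36 for r = 0.2, 0.3 and 0.4. The visit term is significant in about 30%, 58% and 85% of trials, the contrast in about 5%. With SD of L = 0.5 and the smaller residual, the visit-term figures are 21%, 42% and 67%.

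**Second illustration, with a different assumed curve and variances (80 participants).** Rejection rates for the visit term against the three-way test: null, 4.7% and 4.4%; pure level shift, 85% and 5%; change in curve shape with unchanged mean, 5% and 96%; change in the rise only, 46% and 84%. The pattern is the same, although here the omnibus three-way test does well, so its power depends heavily on the assumptions.

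**The case against.** A reader might infer that the model excludes timepoint. The text does not say so. SCFA change is entered into a mixed model that can already carry timepoint, the word introducing the visit interaction does not make the list exhaustive, and SCFA change may simply take the place of group throughout. A condensed article may leave the full list of terms to the analysis plan. This stands: the omission is one of naming, and a reader cannot tell which term will be tested.

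The outcome might also be a per-visit response summary, in which case the visit interaction is the right term. The article does not settle this, so the point is conditional on raw samples being the outcome.

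A reader might further infer that the named term says nothing about the stress response. That is too strong. Post-stress samples enter the mean, so the term has some power for a pure change in the rise (39% and 46% in the closest scenarios above), and for group the protocol itself treats the visit interaction as a principal effect.

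The re-feeding argument has limits. Under Baseline and post-intervention visit, low-fibre meals are standardised before and on each visit day, which may reduce diet-driven differences in SCFA. Nor does the Background section say that renourishment changes only basal cortisol. If it also changes reactivity, a baseline-corrected contrast would be confounded too. The fix therefore separates level from response but does not remove confounding.

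Finally, adding the three-way term and using a summary measure are not interchangeable. In the first illustration the 7-df test had about half the power of the single contrast.

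**Conclusion.** The point holds in limited form. For this supplementary model the article states a stress-response target and names only an interaction with visit. On raw samples, that interaction is a contrast of mean cortisol level. It responds to a basal shift between visits and, when levels vary between visits, loses power for a change in the stress-induced rise.

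The algebra is firm given raw, sample-level cortisol as the outcome. The percentages are not estimates for this trial: responder rate, curve, variances and correlations are all assumed, and without level variation the loss of power disappears.

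It would be wrong to carry this over to the primary analysis. The randomised comparison names its group-by-visit-by-timepoint effect and is untouched. The issue should be corrected before analysis, but it bears only on the mechanistic interpretation.

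**What to change.** State the cortisol outcome and the tested effect for this model. Either:

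- use a pre-specified baseline-corrected response per visit (area under the curve with respect to increase, or post-stress peak minus pre-stress) and test its association with SCFA change through the visit interaction; or
- keep the raw samples, add SCFA-change-by-visit-by-timepoint, and test the matching 1-df post-stress-minus-pre-stress contrast within it.

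In either case, report SCFA-change-by-visit on the raw samples separately, labelled as overall cortisol level.

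The cost is at most one extra model term and a sentence or two of text, with no new data. The omnibus 7-df test should not be the tested effect, since it can have less power than the single contrast. The samples that form the contrast should be fixed before unblinding.

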### Study design and setting

This study is a monocentric, randomized, triple-blind, placebo-controlled trial with two parallel arms. Participants in both groups will receive concomitant treatment as usual, consisting of an inpatient psychotherapeutic program of 12 weeks focusing on nutritional rehabilitation. Using a block randomization method, we will randomly assign participants to the placebo or SCFA group with a 1:1 allocation ratio. The total duration of the study is 12 weeks, including a pre-intervention baseline visit, which takes place within the first week of hospitalization, a post-intervention visit at six weeks, and a follow-up visit at 12 weeks. The study will be conducted at the Leuven University Psychiatric Hospital (UPC Z.Org), Belgium.

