### Sample size

Based on our previous work [19], we calculated, using the General Linear Multivariate Model Power and Sample Size software (GLIMMPSE), that a total sample size of 70 participants (n = 35 per treatment arm) yields sufficient power (80%) to detect the previously found effect of SCFAs on the cortisol response to an acute stress paradigm. Given that no information is available to calculate the effects of SCFAs on stress-induced cortisol response in patients with AN where greater variability might be present, we increased the sample size to 80 participants (n = 40 per arm). Based on a sensitivity power calculation (G*Power 3.1.9.2 software), 40 participants per arm would enable us to achieve 80% power to detect a small effect (Cohen's f = 0.16) in a within-between 2 (“visit”, baseline vs. post-intervention) × 2 (“treatment”, placebo vs. SCFA) mixed ANOVA model. Taking into consideration a 15% risk of dropout, we aim to recruit 92 individuals in total.

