### Interventions and concomitant care

We will efficiently deliver SCFAs to the large intestine by utilizing pH-dependent CDCs to mimic the process of dietary fiber fermentation in the colon, as done previously [19]. Participants will consume capsules of a mixture of SCFAs spread at four intervals throughout the day. The SCFA mixture contains acetate, propionate, and butyrate in a ratio of 60:20:20, and the total daily amount of SCFAs is equivalent to the fermentation of 10 g of arabinoxylan oligosaccharides [38]. Microcrystalline cellulose, not absorbed in the gastrointestinal tract, will be included in the same type of CDCs to serve as a placebo. The nursing staff will distribute the capsules to the participants individually, supervise their intake, and monitor adherence by capsule count. Although adverse effects are not expected [19], these will be documented. Participation will be discontinued if the patient exhibits a high medical or psychiatric risk requiring priority or fails to adhere to the consumption of the intervention substances (taking less than 80% of capsules) or to the study procedures.

Participants in both groups will receive treatment as usual, consisting of an inpatient psychotherapeutic program of 12 weeks focusing on nutritional rehabilitation. We will closely monitor the use of other medications throughout the study. However, such usage will not lead to the termination of the trial intervention. After undergoing the intervention and post-intervention visit, if any participant decides to leave the residential program early, we will still aim for a follow-up visit to take place at the hospital.

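### The AN-subtype analysis uses only the SCFA arm, so a subtype difference in course under usual care would pass for a subtype difference in the SCFA effect

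*Protocol article*

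**What the plan says.** The section Statistical methods for primary and secondary outcomes builds the main inference on both arms: "The group-by-visit and the group-by-visit-by-timepoint interaction effects constitute the principal effects of interest". For the subtypes it departs from this: "Data of the intervention group will be further exploratively analyzed using linear mixed models with restrictive type AN and binge/purge type AN" as the patient-group factor. The stated purpose is "investigating differences between the intervention of SCFAs between subtypes of patients with AN". Both the data set (SCFA arm only) and the question (does the SCFA intervention act differently by subtype) are therefore written down. No other section gives a subtype model that includes placebo patients.

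Two sections describe care common to both arms. Study design and setting states: "Participants in both groups will receive concomitant treatment as usual, consisting of an inpatient psychotherapeutic program of 12 weeks". Interventions and concomitant care repeats this and adds the aim of the programme: "Participants in both groups will receive treatment as usual, consisting of an inpatient psychotherapeutic program of 12 weeks focusing on nutritional rehabilitation".

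**The concern.** The question is one of effect modification: is SCFA minus placebo different in restrictive-type and binge/purge-type patients? Without placebo patients, the model can only compare how much treated patients of each subtype changed between visits. That change includes everything else that happens over six weeks: the response to inpatient refeeding and psychotherapy, a second exposure to the stress test, and regression to the mean. If any of these differs by subtype, the difference enters the subtype contrast in full.

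The trial does hold the data to remove it. Placebo patients of each subtype go through the same programme and the same visits, and subtracting their change isolates the SCFA part. The plan sets them aside for this one question. A subtype finding from the treated arm alone could not be attributed to SCFA, and the absence of a finding could equally hide a real difference masked by an opposite natural course.

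**Working it through.** **1. The plan's own figure.** The article gives no figure for the subtype analysis. Its nearest figure, in Sample size, is that "40 participants per arm would enable us to achieve 80% power to detect a small effect" (Cohen's f = 0.16) in a 2 × 2 within-between model. With N = 80, m = 2 visits and an assumed correlation ρ between visits of 0.5 (not stated in the article):

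λ = f²·N·m/(1 − ρ) = 0.0256 × 80 × 2/0.5 = 8.19, on 1 and 78 df, giving power 0.807.

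This reproduces the stated 80%. With ρ = 0.3 or 0.7 the power would be 0.67 or 0.95. The 40 patients per arm carry over to the steps below.

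**2. What the one-arm contrast estimates.** Let *d* be the subtype difference in pre-to-post change under usual care, and *m* the subtype difference in the SCFA effect.

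- SCFA arm: the subtype difference in change is *m* + *d*.
- Placebo arm: the subtype difference in change is *d*.
- SCFA arm minus placebo arm: *m*.

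The planned analysis estimates the first line and the stated question concerns the third. The bias is exactly *d*, whatever the sample size.

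**3. How often this misleads.** Inputs:

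- 40 evaluable patients per arm (Sample size).
- "The chosen significance level is alpha = 0.05", taken as two-sided.
- Assumed: SD of change = 1, *m* = 0, subtype split between 50:50 and 70:30, and *d* from 0 to 0.8 SD.

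Standard errors of the subtype contrast:

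- One arm, 20 vs 20: √(1/20 + 1/20) = 0.316. One arm, 28 vs 12: √(1/28 + 1/12) = 0.345.
- Two-arm interaction: √2 times these, that is 0.447 and 0.488.

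The one-arm test has a noncentral t distribution with 38 df and noncentrality *d*/SE. At 20 vs 20 this is *d*·√10, for example 0.5 × 3.162 = 1.58.

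| *d* (SD of change) | SCFA arm only, 20 vs 20 | SCFA arm only, 28 vs 12 | Both arms, interaction |
|---|---|---|---|
| 0 | 5.0% | 5.0% | 5% |
| 0.2 | 9.5% | 8.7% | 5% |
| 0.3 | 15.2% | 13.5% | 5% |
| 0.5 | 33.8% | 29.2% | 5% |
| 0.8 | 69.3% | 61.8% | 5% |

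Entries are the probability of a significant subtype difference when the SCFA effect is the same in both subtypes.

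**4. Simulation.** In 20,000 simulated trials at each of *d* = 0, 0.3, 0.5 and 0.8, with 20 patients per subtype per arm, the one-arm test rejected in 5.2%, 15.2%, 33.8% and 69.8%, with a mean estimate equal to *d* to within 0.002. The two-arm interaction rejected in 4.8% to 5.2%, with a mean estimate within 0.004 of zero.

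**5. Price of the valid contrast.** The subtype difference detectable with 80% power rises from 0.91 to 1.27 SD at 50:50, and from 0.99 to 1.38 SD at 70:30.

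**The case against.** The strongest reply is that the analysis is labelled exploratory. It touches neither the primary outcome, nor the principal interactions, nor the sample size, and subtype is not among the stated hypotheses. That limits the consequences. It does not turn a one-arm contrast into an estimate of effect modification.

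A second reply is that the purpose clause is loosely worded and could mean only a description of how treated patients of each subtype change. Such a description would be legitimate. However, the text speaks of differences in the SCFA intervention, and the natural reading is a difference in its effect. If description is meant, the wording has to say so.

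Third, the rates rest on assumptions. The article reports no subtype mix and no evidence that the subtypes differ in course. It also cites an absence of habituation to repeated stress tests given a sufficient interval. Uneven splits lower the rates, as the table shows, and excluding cortisol non-responders would lower them further by shrinking the sample. The calculation also reduces the mixed model to a single change score. All of this affects the size and none of it affects the identification problem: the bias remains *d*.

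Finally, the valid interaction is weak, with only differences well above 1 SD reliably detectable. This is true, and it argues for reporting estimates with intervals. It does not justify a more precise estimate of a different quantity.

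**Conclusion.** The concern holds. The article fixes a data set that cannot answer the question it sets: the SCFA arm alone yields the difference in SCFA effect plus the difference in usual-care course, and the two cannot be separated. That conclusion needs no numerical assumption.

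The size does. With 40 evaluable patients in the arm, splits from 50:50 to 70:30 and natural-course differences of 0.3 to 0.8 SD, a subtype difference that does not exist is declared in about 14% to 69% of trials instead of 5%. If the subtypes share the same natural course, the error rate is the nominal 5%, but data from the SCFA arm alone cannot show whether that is so. The damage is confined to an exploratory analysis and leaves the primary conclusion intact. The plan should still be corrected, because as written any subtype statement about SCFA would be uninterpretable.

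**What to change.** Replace the subtype sentence with a model fitted in both arms that contains the group × visit × subtype interaction (× timepoint where the outcome is measured repeatedly within a visit), together with all lower-order terms. Report the SCFA-minus-placebo effect within each subtype and the difference between them, each with a confidence interval, labelled exploratory and not judged by significance.

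If the team prefers to keep the SCFA-arm model, the smaller change is to describe it as a comparison of course among treated patients and to draw no conclusion about a differential SCFA effect. This is a fallback, since it leaves the stated question unanswered.

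The cost is one sentence, with no new data. The downside is precision: the interaction's standard error is √2, about 1.4, times that of the one-arm contrast, so the intervals will be wide. The change should be made before unblinding, so that it cannot appear driven by results.
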